#### Demographic and anthropometric measures

During their baseline visit, participants will be asked about their age, ethnicity, smoking status, dependents, marital status, education level, current job role and grade, working hours, length of time in post in the NHS, postcode and household composition. At each follow up visit, participants will be asked if there has been any change in these measures. At baseline and each follow up visit, participants will have their height, weight, waist circumference (WC), blood pressure (BP) and body fat percentage measured. Height will be measured to the nearest centimetre using a Leicester portable height measure. Weight, in kilograms, and body composition will be measured using a Tanita Body Composition Analyser (Tanita UK Ltd, Middlesex, UK). Participants will be asked to remove shoes, socks and heavy outerwear clothing and to ensure their pockets are empty before stepping on to the scales. Body mass index (BMI) will be calculated by the scales as kg/m^2^. WC will be measured to the nearest centimetre (cm) using a standard anthropometric tape measure, with the tape measure being placed around the abdomen midway between the uppermost border of the iliac crest and the lower edge of the chest (thorax) formed by the bottom edge of the rib cage. BP will be assessed using an Omron M6 automated blood pressure monitor (Omron Healthcare Europe, Hoofddorp, Netherlands). Participants will be asked to sit quietly and relax prior to having their BP measurements taken and three readings will be taken.

At baseline and 12 months follow up participants will have point of care testing (POCT) for the measurement of HbA1c, triglycerides, glucose, total cholesterol, HDL cholesterol and calculated LDLc. Capillary blood samples will be taken from each participant using the finger prick method. The CardioChek® system, which is a portable hand-held device that requires between 15–40 μL (millions per microliter) of blood taken using a finger-stick, will be used for these measurements. No blood will be stored and all blood contaminated testing sticks will be deposed of appropriately. All participants will receive feedback on these results. If any of the values for these measures appear to be outside of the normal range or raise concern with the research team, results will be checked by a medic. Participants will be advised to contact their GP and a letter will be sent to their GP detailing the results.

#### Work-related health measures

Various measures will be employed in order to characterise work-related health:Job performance [41] and job satisfaction [42] will be measured using single-item 7-point likert scales, and participants will also be asked to indicate the extent to which they intentionally changed their work priorities and objectives to accommodate the change from sitting behaviour (6-point fully anchored scale).Work engagement (characterized by vigour, dedication, and absorption) will be measured using the Utretcht Work Engagement Scale (UWES) [43]; a multi-item 7-point likert scale.Occupational fatigue will be measured using the Need for Recovery (NFR) Scale [44].In order to assess self-reported ratings of symptoms most often encountered in an occupational setting the Standardised Nordic Questionnaire (SNQ) for the analysis of musculoskeletal symptoms [45] will be used.Work-related cognitive function will be assessed using an experimental cognitive test battery including measures for memory recall [46], verbal fluency [47], attention [48], information processing (digit-symbol substitution task) [49, 50] and executive function [51].Data on sickness absence will be collected using both self-report and from employer records and include frequency and duration of self-certified and certified sickness. Reasons for sickness absence will also be recorded. Data on sickness absence will be collected for 12 months prior to the intervention and for the 12 months of the intervention and follow-up period.Presenteeism will be assessed both by using the 8-item Work Limitations Questionnaire [52] that asks participants to rate on a six-point Likert scale how their health has affected aspects of their work in the past two weeks, and the Work Productivity and Activity Impairment Questionnaire (WPAI-GH 2.0) [53].Participant's sleep duration and quality will be assessed using the Pittsburgh Sleep Quality Index (PSQI) [54].Finally, to assess participant’s perceptions of work and job demands, the Health and Safety Executive Management Standards Indicator Tool (HSE MSIT) [55], which uses a 5-point likert scale for participants to reflect their work over the last 6 months, will be administered.

#### Psycho-social measures

A mix of qualitative and quantitative psychosocial measures will be employed at baseline, 3, 6, and 12 months to identify behavioural self-efficacy (based on the application of the Theory of Planned Behaviour [56], acceptability and awareness of environmental and organisational change, strength of ‘habit’ in workplace behaviours, including sitting (modified Self-Report Habit Index) [57]; while mood/affective states will be measured using the Multiple Affect Adjective Checklist-Revised [58]. A general assessment of quality of life will be conducted using the WHOQOL-BREF [59].

#### Subjective sitting time

Participants will be asked to complete the Workplace Sitting Breaks Questionnaire (SITBRQ) [60], a 2-part question, asking about the amount of breaks from sitting an individual will take during a typical hour at work and roughly the amount of time spent in short physical activity breaks across a typical work day.

For a complete list of outcomes and scheduled measurements, see Table 1.

**Table 1 Tab1:** Schedule of the outcome measures

Measure	Baseline	3 months	6 months	12 months
Objective siting time and physical activity (activPAL and wrist accelerometer)	✓	✓	✓	✓
Office/desk dwell time (proximity-based location devices)	✓	✓	✓	✓
Job performance	✓	✓	✓	✓
Job satisfaction	✓	✓	✓	✓
Work engagement (UWES)	✓	✓	✓	✓
Occupational fatigue (NFR)	✓	✓	✓	✓
Habit (SRBAI)	✓	✓	✓	✓
Musculoskeletal symptoms (SNQ)	✓	✓	✓	✓
Cognitive function tests	✓	✓	✓	✓
Self-reported workplace sitting (SITBRQ)	✓	✓	✓	✓
Presenteeism (WLQ and WPAI-GH 2.0)	✓	✓	✓	✓
Self-efficacy	✓	✓	✓	✓
Mood/affective states (MAACL-R)	✓	✓	✓	✓
Quality of Life (WHOQOL-BREF)	✓	✓	✓	✓
Sleep Quality (PSQI)	✓	✓	✓	✓
Work and Job Demands (HSE MSIT)	✓		✓	✓
Self-reported sickness absence	✓			✓
Sickness absence via employee records	✓			✓
Anthropometric measures	✓	✓	✓	✓
Blood samples	✔			✔

#### Cost analysis

Cost effectiveness will be undertaken following guidelines from the World Health Organisation (WHO) [61]. Programme input costs will be calculated based on the time cost of additional organisational meetings and adjustment of workspace, the cost of desks and physical changes to the workspace and any disruption to normal working patterns, including reasonable allocation of (joint) costs imposed on other activities as a result of the planned changes. Any costs associated with subsequent additional arrangements required to ensure that the process of changed work patterns proceeds would be included. Such costs can then be compared across the control and treatment groups for any array of measures of the output of the intervention such as sickness absence and job performance. Costs will be suitably discounted across time.

#### Process evaluation

A process evaluation will be undertaken to understand the influence of SMArT Work on the study outcomes, to ascertain what elements of the intervention were favoured by the members of staff and to help inform future development. We will use a variety of techniques to gather information on recruitment, data collection, deviations from the protocol, delivery of the intervention and data on environmental factors which may impact on the study.

Interviews will be conducted with a subset (~20) of intervention participants at 12 months to gain additional insight into the perceptions of those that received the intervention and identify what aspects of the intervention worked for them, what was useful and what was not. A topic guide will be used to facilitate the process of data collection, but this will be used flexibly with scope for discussion of additional relevant topics that may arise. Interviews will be audio recorded and transcribed verbatim. Analysis will be iterative and informed by the constant comparative method. Preliminary open codes will be generated from the first few interviews. Ongoing analysis will lead to the development and refinement of the codes into a coding framework. Analysis will be facilitated using a fully-licensed custom software application (NVivo8, a qualitative data-indexing package).

We will also provide participants with disposable cameras to take photos of their workstation and office space at each time point in order to inform a picture content analysis. Such procedures will be carried out for all implemented intervention strategies, as well as work-related meaningful events (contractual changes, managerial/staff changes, policy changes, workload changes).

#### Statistical analysis

A statistical analysis plan will be written and agreed by all investigators before the final data become available for analysis. Cluster and participant level characteristics will be compared by group allocation, using either means (SD) or medians (IQR) for continuous variables, and counts and percentages for nominal variables. The primary outcome, occupational sitting time at 12 months, will be analysed initially on a complete case basis. To adjust for clustering, sitting time will be analysed using generalised estimating equation models with an exchangeable correlation structure and an identity link with a normal distribution. The models will include allocated group and baseline value as covariates. All secondary outcomes, including sitting time at 3 and 6 months, will be analysed using the same method. Sensitivity analyses will be carried out for the primary outcome. The analysis will be repeated imputing any missing values for sitting time using multiple imputation (ITT).

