#### Sample size

To detect a difference in objectively measured sitting time of 60 min, assuming a SD of 60 min, 90 % power and 5 % alpha we would require 22 participants per arm, if the trial was individually randomised. As this is a cluster randomised trial, this sample size needs to be inflated to take into account the clustering. Assuming an average cluster size of 13 (varying between 3–50, therefore CV = 0.9) and an intraclass correlation coefficient of 0.05 gives a design effect of 2.13, resulting in 65 participants from 5 clusters per arm. To conform to best practice we have increased the sample size to take into account both drop out at the cluster and participant level. Therefore we will recruit 17 participants per cluster, this allows for the primary outcome data to be unavailable for 25 % of participants. Increasing the number of clusters by one per arm therefore gives a total of 7 clusters per arm each recruiting 17 participants on average (7*17*2 = 238), giving 238 participants in total. Exact cluster sizes may be modified after the first phase of the project (focus groups, intervention development).

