#### Randomisation

Randomisation will occur after all baseline assessments and data is collected. Clusters will be randomised 1:1 to either intervention or control groups stratified by office size with a block size of 4. Clusters will be randomised by an independent statistician.

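### Clusters are randomised within office-size strata, but the stated GEE covariates leave office size out; adding it, with a small-sample correction, is a minor improvement

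*Protocol article*

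**What the plan says.** Randomisation: "Clusters will be randomised 1:1 to either intervention or control groups stratified by office size with a block size of 4". The number of strata, their cut-points and the reason for choosing office size are not given.

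Statistical analysis: sitting time is analysed with "generalised estimating equation models with an exchangeable correlation structure and an identity link with a normal distribution". On covariates: "The models will include allocated group and baseline value as covariates". On the rest: "All secondary outcomes, including sitting time at 3 and 6 months, will be analysed using the same method". Multiple imputation is planned as a sensitivity analysis of the primary outcome. Office size does not appear anywhere in the analysis, and no reason is given for leaving it out.

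A separate statistical analysis plan is promised. The article does, however, state the covariate list, so this is a stated choice and not an item left open.

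**The concern.** Stratified allocation tends to balance office size between the arms, which takes between-stratum variation out of the true sampling variance of the arm difference. A model without the stratum leaves that variation in the residual between-cluster variance. If the variance estimator is otherwise valid, the reported standard error then exceeds the true one, the test falls below its nominal level, and the precision bought by stratifying is not used.

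At stake are interval width and power for effects smaller than planned, in a trial with only 14 clusters. The same holds for the secondary outcomes, which inherit the model. All of this depends on office size predicting follow-up sitting after adjustment for baseline.

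**Working it through.** **Inputs from the Protocol article (Sample size).** Difference 60 min, SD 60 min, 90 % power, 5 % alpha, average analysed cluster size 13, CV 0.9, ICC 0.05, 7 clusters per arm, 17 recruited per cluster, 25 % missing (17 × 0.75 = 12.75, about 13 analysed).

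**Assumed, not in the documents.** Two strata of 8 small and 6 large offices; correlation of 0.5 between baseline and follow-up; a true effect of 30 min as the smaller effect of interest; the size of any office-size gap.

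**1. The plan's own figures.** n per arm = 2 × (1.96 + 1.2816)² × (60/60)² = 21.01, rounded up to 22. Design effect = 1 + ((1 + 0.9²) × 13 − 1) × 0.05 = 2.1265. Both agree with the stated 22 and 2.13.

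**2. Variance available to the stratum.** Between-cluster variance = 0.05 × 60² = 180; within-cluster = 3420. A gap g between the strata contributes g² × (8/14) × (6/14) = 0.245 g².
- g = 20: 98, or 54 % of 180.
- g = 30: 220, more than the whole 180. Added on top, it gives an ICC of (180 + 220)/(180 + 220 + 3420) = 0.105.
- Largest gap compatible with ICC 0.05: √(180/0.245) = 27 min, and only if office size explains all the clustering.

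**3. Analytic standard error, no baseline covariate.** With 7 × 13 = 91 analysed per arm and a share f of the between-cluster variance explained by the strata:

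SE = √{2 × [3420 + 180 × (1 − f) × 13 × 1.81] / 91}

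The model without the stratum reports the f = 0 value, 12.97 min, so it rejects when the estimate exceeds 1.96 × 12.97 = 25.42. The true SD is the SE at the actual f.

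| f | True SD (min) | SE overstated by | Actual type I error | Power at 30 min, stratum omitted: Φ((30 − 25.42)/SD) | Power at 30 min, stratum included: Φ(30/SD − 1.96) |
|---|---|---|---|---|---|
| 0 | 12.97 | 0 % | 5.0 % | 64 % | 64 % |
| 0.25 | 12.04 | 8 % | 3.5 % | 65 % | 70 % |
| 0.50 | 11.03 | 18 % | 2.1 % | 66 % | 78 % |
| 0.75 | 9.92 | 31 % | 1.0 % | 68 % | 86 % |

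At 60 min, power is at least 99.6 % in every row. With only 5 clusters of 13 per arm, SE = √(7200 × 2.1265/65) = 15.35 and power at 60 min is Φ(60/15.35 − 1.96) = 97.4 %. The table is an upper range: it uses a normal reference, charges nothing for lost degrees of freedom, and ignores the planned baseline covariate, which absorbs part of any lasting office-size difference.

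**4. Simulation with the baseline covariate.** 14 clusters, exchangeable GEE, Mancl-DeRouen standard error, t(12) without the stratum and t(11) with it, true effect 30 min:

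| Office-size effect | Without stratum | With stratum |
|---|---|---|
| None | 68 % | 63 % |
| 15 min, same gap at baseline, total ICC 0.05 | 73.6 % | 71.4 % |
| 20 min, absent at baseline, total ICC 0.05 | gain of about 8 points with the stratum | |

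Power at 60 min is about 99 % with either model. The runs used 800 to 1,200 replicates, so one power figure has a Monte Carlo error of about 1.5 points (√(0.7 × 0.3/1000) = 0.014).

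**5. The variance estimator.** In a simulation without a baseline covariate at f = 0.50, the uncorrected sandwich SE was 10.1 against a true SD of 10.9 without the stratum, and 8.4 against 11.0 with it. Type I error under a normal reference was 12.9 % and 19.5 %. Averaging the uncorrected and Mancl-DeRouen variances, with a t reference, gave 5.2 % and 8.0 %. Adding the stratum alone would therefore make an uncorrected analysis more anti-conservative.

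**The case against.** The strongest reply is that the plan's own baseline covariate already does most of the work. A lasting difference between small and large offices would show in baseline sitting. When the simulated gap is present at baseline, the stratum gains nothing or costs a little. If office size is irrelevant, adding it costs about 5 points of power at 30 min. The primary conclusion at 60 min is safe either way, and any error from the omission itself is conservative. All of this stands, and it limits the point to a minor one.

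It can also be said that the protocol gives no reason for stratifying by office size. Balancing participant numbers between arms, with clusters expected to range from 3 to 50, is as natural a purpose as an expected difference in sitting. That also stands.

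What the reply does not remove is the mismatch between a stratified allocation and a stated model that ignores it. Nor does it exclude an office-size effect that emerges only at follow-up. Also, 14 clusters do not fill blocks of 4 (14 = 3 × 4 + 2), so at least one block is incomplete and balance on office size is not guaranteed. Adjustment covers that case.

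**Conclusion.** The point holds as a minor design–analysis mismatch. If office size predicts follow-up sitting beyond baseline, a validly corrected standard error without the stratum is conservative. Under the assumptions above, the effect of adding the stratum on power at 30 min runs from a loss of about 2 to 5 points to a gain of about 8. At 60 min it makes no practical difference. The number of strata and the office-size effect are unknown, so confidence in any particular size is limited.

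Three stronger readings are tempting but not supported.
- **A loss of about 20 power points.** This needs a 30 min gap that is absent at baseline. Such a gap alone exceeds the between-cluster variance implied by the plan's ICC and doubles the ICC to about 0.105.
- **Standard errors that are simply too large.** That presumes a small-sample correction. The article states none, which may be left to the analysis plan, and an uncorrected sandwich error with 14 clusters runs too small.
- **A biased estimate, or a stratifier chosen because sitting differs by office size.** Neither follows from the document.

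**What to change.** State in Statistical analysis that the covariates are the allocated arm, the baseline value and the office-size category under which the cluster was randomised. Use the category fixed at randomisation, not the cluster size achieved. Apply this to the primary outcome and all secondary outcomes, and include the category in the imputation model. In the same edit, specify a small-sample-corrected GEE standard error with a t reference distribution. The analysis plan should name the correction, since the averaged one in the check still gave about 8 % type I error with the stratum included.

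The category is already held by the randomising statistician, so no new data are needed. The cost is one of about 12 between-cluster degrees of freedom for each stratum beyond the first (12 to 11 with two strata, 12 to 10 with three), and a small loss of power if office size turns out not to matter. Settling it before the final data are available also removes a later choice between adjusted and unadjusted results.

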## Discussion

There is accumulating evidence demonstrating the health risks of high levels of sedentary behaviour, with substantial epidemiological evidence illustrating the high proportion of time spent in sitting behaviours in office-based workers. To address excessive sitting as a potentially independent health risk, high quality intervention studies are necessary for determining feasibility, effectiveness and sustainability of these interventions for reducing workplace sitting time. With a lack of large scale, long term RCTs, the primary aim of the SMArT Work trial is to develop a workplace intervention to reduce prolonged sitting over 12 months.

The strengths of the project are the community based participatory research approach in the development of a randomised controlled trial. The robust study design has baseline, 3, 6, and 12 month follow up to assess short, medium and long term behaviour. Additionally, a process evaluation, including a cost analysis, will be an integral part of this trial to ascertain not only if the intervention is effective in reducing occupational sitting time, but also to understand why the intervention is, or is not, feasible and sustainable for future uptake in the NHS or other employers. Finally, this study uses an objective measure of sedentary behaviour for its primary outcome.

The results of this intervention will provide insight for future studies and offer evidence for policy guidelines around workplace health and well-being.

## Abbreviations

BCT: Behaviour change technique
BCW: Behaviour Change Wheel
BMI: Body mass index
BP: Blood pressure
CBPR: Community-based participatory research
COM-B: Capability, opportunity, motivation - behaviour
CONSORT: Consolidation Standards of Reporting Trials
CVD: Cardiovascular disease
GP: General practitioner
HSCIC: Health and Social Care Information Centre
HSE MSIT: Health & safety executive management standards indicator tool
IF: Intervention function
IQR: Interquartile range
ITT: Intention to treat
LPA: Light physical activity
MAACL-R: Multiple affect adjective checklist - revised
MVPA: Moderate to vigorous physical activity
NFR: Need for recovery scale
NHS: National Health Service
POCT: Point of care testing
PSQI: Pittsburgh Sleep Quality Index
RCT: Randomised controlled trial
SBRN: Sedentary Behaviour Research Network
SD: Standard deviations
SITBRQ: Workplace Sitting Breaks Questionnaire
SNQ: Standardised Nordic Questionnaire
SRBAI: Self-report behavioural automaticity index
TDF: Theoretical Domains Framework
UHL: University Hospitals of Leicester
UWES: Utrecht work engagement scale
WC: Waist circumference
WHO: World Health Organisation
WHOQOL BREF: WHO quality of life - brief
WLQ: Work Limitations Questionnaire
WPAI-GH: Work productivity and activity impairment questionnaire: general health
